### 2.11. Statistical Analysis

A statistician independent of the trial procedure and assessment will conduct statistical analysis using SAS^®^ Version 9.4 software (SAS Institute Inc., Cary, NC, USA). In principle, for effectiveness analysis, a full analysis set of all randomly assigned participants who are evaluated at least once after receiving a prescription of investigational products at least once will be conducted, according to intention-to-treat analysis. If necessary, per-protocol set (PPS) analysis will be performed, including participants who have completed the entire process of the clinical trial and have no significant violations affecting the test results. Participants with less than 70% compliance with the investigational product, taking prohibited drugs for the treatment and management of diseases other than gastrointestinal disease under the judgment of investigators, or experiencing events that can cause digestive symptoms such as sudden stress during the clinical trial period, will be excluded from the PPS analysis. Safety analysis will include all data obtained from participants who have taken at least one investigational product in the YGJ and PWS groups and all participants in the usual care group.

The demographic characteristics of participants will be summarized by group. Continuous data will be presented as mean and 95% confidence intervals (CIs), whereas dichotomous data will be displayed as frequency and percentage. The primary outcome of this study is the difference in the TDS score at week 6 between the YGJ and usual care groups (Hypothesis 1).

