## Abstract

The herbal medicine Yukgunja-tang has been widely used for the treatment of functional dyspepsia (FD) in the clinical setting of East Asian traditional medicine. This paper presents a protocol for a randomized, assessor-blind, controlled, multicenter, three-arm parallel clinical trial comparing the effectiveness, safety, and cost-effectiveness of Yukgunja-tang with Pyeongwi-san and usual care. A total of 140 participants with Rome IV-diagnosed FD will be randomly assigned to either the Yukgunja-tang (n = 56), Pyeongwi-san (n = 56), or usual care (n = 28) groups. All participants will be educated on dietary guidelines for FD patients. Participants in the Yukgunja-tang and Pyeongwi-san groups will take investigational products for 6 weeks. All participants will be assessed for clinical parameters at weeks 0, 3, 6, 9, and 24. The primary outcome will be measured on the total dyspepsia symptom scale, and the secondary outcome will include the single dyspepsia symptom scale, overall treatment effect, the visual analog scale for dyspepsia, FD-related quality of life, hospital anxiety and depression scale, EuroQol-5 dimension, pattern identification, and serum levels of acyl-ghrelin and deacyl-ghrelin. Adverse events and laboratory tests will be monitored for safety assessment. The results will provide evidence of the effectiveness, safety, and cost-effectiveness of Yukgunja-tang in the treatment of FD.

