During the clinical trial period, dietary guidelines based on dietary recommendations prepared for Korean dyspepsia patients [20] will be distributed and explained to all participants in the three groups. The usual care group will perform daily management while following the dietary guidelines distributed during the clinical trial period without administration of any investigational product. Under the judgement of the investigator, medications and treatments other than those prohibited in this clinical trial may be permitted, and all medications and treatments performed during the trial period should be recorded in the CRF. YGJ and PWS groups are also allowed to perform usual care.

Concomitant medications are permitted only if the investigators determine that they do not affect the outcomes of this study, including drugs used to treat underlying diseases or therapeutic drugs in case of adverse events. The investigators will check and record all the detailed information of concomitant medications in the CRF. During the entire trial period, participants are prohibited from taking medications, including proton pump inhibitors, histamine receptor antagonists, antacids, prokinetics, antidepressants, gastric fundus relaxants, gastric mucosal protectants, nonsteroidal anti-inflammatory drugs, anticholinergics, oral corticosteroids, and treatment regimens for *Helicobacter pylori*, which, in the opinion of the investigators, may affect the gastrointestinal tract. In addition, it is prohibited to receive Korean medicine treatments such as acupuncture, herbal medicine, or moxibustion for the purpose of improving indigestion during the clinical trial period.

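### The full analysis set requires a prescription of investigational product, so read literally it admits none of the 28 usual care participants

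*Protocol article*

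**What the plan says.** Section 2.11 of the protocol article defines one population for effectiveness: "all randomly assigned participants who are evaluated at least once after receiving a prescription of investigational products at least once". It says that this analysis "will be conducted, according to intention-to-treat analysis". It gives no other entry condition for any arm.

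Section 2.8 describes usual care as dietary guidance and daily management "during the clinical trial period without administration of any investigational product". The Abstract agrees: "Participants in the Yukgunja-tang and Pyeongwi-san groups will take investigational products for 6 weeks". In Table 1 the product row carries the symbol reserved for the YGJ and PWS groups.

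The safety population, later in the same paragraph of section 2.11, is written by arm. It takes in participants who have taken "at least one investigational product in the YGJ and PWS groups and all participants in the usual care group".

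On the per-protocol set the section says: "If necessary, per-protocol set (PPS) analysis will be performed". It states no trigger for that decision.

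**The concern.** Hypothesis 1 (YGJ against usual care, primary) and Hypothesis 2 (PWS against usual care) both need the usual care arm. The effectiveness population sets an entry condition that this arm cannot meet. Under the fixed sequence in section 2.11, Hypothesis 3 is reached only through Hypotheses 1 and 2, and its margin is taken from the Hypothesis 2 confidence interval. A literal application therefore stops the whole confirmatory sequence.

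In practice someone will repair the rule. The obvious repair keeps the prescription condition for the two herbal arms and waives it for usual care. Section 2.7 says that participants cannot be blinded, and section 2.6 has the envelope opened in front of them. A condition applied after allocation in two arms out of three does not fit an intention-to-treat label. If the repair is left until data are seen, who counts in the primary analysis becomes a discretionary choice.

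**Working it through.** **1. Apply the rule to each arm (sections 2.8, 2.10 and 2.11, Table 1).**

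| Arm | Randomised | Receives investigational product | Can meet the rule as written |
|---|---|---|---|
| YGJ | 56 | yes, from Visit 2 | yes |
| PWS | 56 | yes, from Visit 2 | yes |
| Usual care | 28 | no | no |

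Excluded by the literal rule: 28 of 140, and 28/140 = 20%. Usual care participants remaining: 28 − 28 = 0. With no controls, neither the Hypothesis 1 nor the Hypothesis 2 contrast can be estimated.

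**2. Check what the plan intends, by reproducing its sample size (section 2.10).** The inputs are a difference of 2.70, SD 3.65, two-sided alpha 0.05, power 80% and a 2:1 ratio of YGJ to usual care.

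- Control n = (1 + 1/2) × [3.65 × (1.960 + 0.842) / 2.70]² = 21.5, rounded up to 22, so YGJ has 2 × 22 = 44. Both match the plan.
- Dropout of 20%: 22/0.8 = 27.5, rounded up to 28. For YGJ, 44/0.8 = 55; keeping 2:1 with 28 controls gives 56. The total is 56 + 56 + 28 = 140, as stated.
- Power with 44 and 22 analysed is 80.9% by the normal approximation and 79.7% by the noncentral t. With all 56 and 28 analysed it is 89.2% (normal approximation).

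The sample size counts 22 evaluable controls, and the analysis-set rule admits none. The two passages cannot both stand. The sample size, the hypotheses and the safety set all point to inclusion.

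**3. Test the obvious repair.** Suppose the prescription condition is kept for YGJ and PWS and waived for usual care, with the evaluation condition kept for all.

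- A participant with no later evaluation is lost in every arm, so this does not differ by arm.
- A participant who is never prescribed product but is later evaluated is dropped in YGJ or PWS and has no counterpart in usual care. Only this group differs by arm.
- Allocation and first dispensing are both at Visit 2, so the group should be small. It is not necessarily empty, because a participant can decline on learning the allocation.

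The shift in an arm mean is the share dropped times the outcome gap between those dropped and those kept. The documents give neither figure. For scale only, assume one such YGJ participant out of 56 whose outcome is worse than the rest by the whole planned effect. The shift is (1/56) × 2.70 = 0.05 points, or 1.8% of 2.70.

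**The case against.** The best defence is that no analyst would run a two-arm trial by mistake. Section 2.10 powers the trial on YGJ against usual care, section 2.11 frames Hypotheses 1 and 2 against usual care, and it also plans to pool the herbal arms against that control. This is also a condensed article, with a fuller protocol and perhaps an analysis plan behind it. The point about intent stands: an empty control arm is what the sentence says, not what the plan wants. Condensation does not excuse the sentence, because the article states the rule rather than deferring it, and the safety population in the same paragraph carries the usual care clause that this one lacks.

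A reader might go further and infer that the informal repair biases the primary comparison by a material amount. The documents do not support that. The condition is receipt of a prescription, not intake, and it bites only on participants never prescribed but later evaluated. Nothing suggests that they are numerous.

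A reader might also infer that the noninferiority test has no protection against dilution from non-adherence. That is too strong. Hypothesis 3 is tested only after YGJ and then PWS differ significantly from concurrent usual care, and the margin is the lower confidence limit of the PWS effect in this same trial. Dilution of both herbal effects makes those steps harder to pass and shrinks the margin. The protection is partial, but it is there. What remains is that the per-protocol analysis, a customary cross-check for noninferiority, is left to an unstated judgement of need.

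**Conclusion.** The concern holds as a defect in a stated rule. As written, the effectiveness population excludes all 28 usual care participants, 20% of those randomised, and Hypotheses 1 and 2 cannot be run on it. The rule must be rewritten before anyone can execute the primary analysis, and this should be done before outcome data by arm are seen.

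The conclusion rests on investigational product meaning the two herbal drugs, which is how section 2.8 and Table 1 use the term. It does not rest on any claim that the sponsor means to leave out the control arm; the rest of the plan shows the opposite.

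Limiting the condition to YGJ and PWS would make the analysis executable but would leave it short of its intention-to-treat label. The numerical effect is probably small and cannot be sized from the documents, so no bias estimate is offered and it does not follow that the randomised comparison is broken. The sample size, hypotheses and tests are unaffected. The unstated trigger for the per-protocol analysis is a secondary matter.

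**What to change.** Redefine the full analysis set in section 2.11 as all randomised participants, analysed in the group to which they were allocated, with a baseline TDS and at least one post-baseline TDS, and with no condition on prescription or intake. The same rule then applies to all three arms. The cost is wording only. Any participant who is never prescribed product but is later evaluated stays in the analysis, as the intention-to-treat label implies.

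As a secondary change, name the per-protocol analysis in advance as a required supporting analysis for Hypothesis 3, replacing the conditional wording. This costs a little more analysis work, and it may give a less favourable noninferiority conclusion if the two populations disagree.

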### 2.7. Blinding

Because it is not possible to blind the participants due to the nature of group assignment, we designed the trial to blind the outcome assessor to minimize the related bias. The effect evaluation of the participants will be conducted by an investigator who will not prescribe the investigational product and will not have access to any source documents, including medical records and case report form (CRF). The outcome assessor only asks questions related to the evaluation items and does not know which group the clinical trial participants are assigned to.

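### The per-protocol analysis of noninferiority is optional, and its analysis set drops participants for undefined stress events linked to the outcome

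*Protocol article*

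**What the plan says.** Section 2.11 of the protocol article makes the full analysis set the default for effectiveness: "In principle, for effectiveness analysis, a full analysis set of all randomly assigned participants who are evaluated at least once". The per-protocol set is conditional: "If necessary, per-protocol set (PPS) analysis will be performed". No condition is given that would make it necessary.

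The per-protocol set is described as participants who completed the trial without important violations. Three grounds for exclusion are then named:

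- a compliance figure under 70% for the study drug;
- a medication ground, worded as "taking prohibited drugs for the treatment and management of diseases other than gastrointestinal disease under the judgment of investigators";
- an event ground, under which those "experiencing events that can cause digestive symptoms such as sudden stress during the clinical trial period, will be excluded from the PPS analysis".

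Under Hypothesis 3, the same section says that noninferiority is tested in the same way as Hypothesis 1, at a 2.5% level. The margin is the lower 95% confidence limit of PWS versus usual care from this same trial (Hypothesis 2). No other analysis set is named for Hypothesis 3, and no rule requires two sets to agree.

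On blinding, Section 2.7 states: "Because it is not possible to blind the participants due to the nature of group assignment". Section 2.6 has the investigator open the allocation envelope in front of the participant. Only the outcome assessor is blinded, and that person has no access to the medical records or the case report form.

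**The concern.** There are two linked weaknesses.

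First, a noninferiority claim is normally examined in both the full and the per-protocol sets, because the two can be biased in different ways. Here the second analysis may be run or not, and nothing prevents that choice from being made after the first result is known. The Introduction and Discussion tie the comparison with PWS to a possible insurance listing for YGJ, so the claim carries weight.

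Second, the per-protocol set would itself be open to bias. A stressful event is not a departure from the protocol by the participant or the site. The clause sets no threshold, time window or list of events. It concerns events that can produce the very symptoms summed in the TDS, so a participant whose symptoms flare is the one most likely to be asked about, and to report, a stressful event. It also conflicts with the trial's own reasoning: the Discussion calls psychological factors closely related to the pathogenesis of functional dyspepsia and gives this as the reason for measuring HADS. Removing stress-related flares removes part of the condition under study, using information that arises after randomisation.

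**Working it through.** **The plan's own figures.** Section 2.10 gives a difference of 2.70, a standard deviation (SD) of 3.65, 5% significance (two-sided in Section 2.11), 80% power and a 2:1 ratio. Usual care needs (1.96 + 0.84)² × 3.65² × (1 + 1/2) / 2.70² ≈ 21.5, so 22, and YGJ needs 44. With 20% dropout, 22/0.8 = 27.5, so 28; 44/0.8 = 55, raised to 56 to keep 2:1. The total is 56 + 56 + 28 = 140. The stated sample size reproduces.

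**Expected margin.** This is the lower limit for PWS versus usual care, with PWS assumed as effective as YGJ, as Section 2.10 does: 2.70 − 1.96 × 3.65 × √(1/n_PWS + 1/n_UC).

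- At 44/22 the standard error is 0.953, and 2.70 − 1.87 = 0.83.
- At 56/28 the standard error is 0.845, and 2.70 − 1.66 = 1.04.

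**Shift from selective exclusion.** Removing k of n participants whose change averages d points below the arm mean moves that mean by k × d / (n − k). The documents give no frequency for stress events, so k and d are assumptions.

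- k = 3, n = 56, d = 3: 9/53 = 0.17 points, which is 20% of 0.83 or 16% of 1.04.
- Extreme bound: if the 3 worst of 45 YGJ participants (about 80% of 56) were dropped, simulation from a normal distribution with SD 3.65 gives a shift of about 0.49 points, over half of 0.83.
- Usual care arm, k = 2, n = 28, d = 3: 6/26 = 0.23 points. This matters if the margin is recomputed within the per-protocol set, because usual care then helps to set it.

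Exclusions in the YGJ arm would ease the claim. Exclusions in the PWS arm would make it harder if the margin is held at one value.

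**Choosing between two sets.** With 56 per arm, a margin treated as fixed and a per-protocol set keeping 70 to 90% at random, simulation gives a one-sided error of 3.3 to 3.8% if either set may support the claim, and 1.2 to 1.7% if both must. The nominal level is 2.5%. The protocol does not say that either set may serve; the figure shows what an unstated rule leaves open.

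**Does dilution in the full analysis set favour noninferiority here?** Assume that 20% of each herbal arm responds as if untreated and that YGJ is truly 1.5 points worse than PWS.

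- The observed deficit falls to 1.5 × 0.8 = 1.2.
- The PWS effect falls to 2.70 × 0.8 = 2.16, so the expected margin at 44/22 falls from 0.83 to 2.16 − 1.87 = 0.29.
- The deficit exceeds the margin by 1.5 − 0.83 = 0.67 before dilution and by 1.2 − 0.29 = 0.91 after it. At 56/28 the excess goes from 0.46 to 0.70.

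The claim gets harder. The algebra shows why: with a same-trial margin the PWS mean cancels, and noninferiority requires YGJ minus usual care to exceed 1.96 × (SE of YGJ−PWS + SE of PWS−usual care) = 1.96 × (0.778 + 0.953) = 3.39 at 44/44/22. Dilution lowers YGJ minus usual care. In simulation of the whole test sequence at 44/44/22, with YGJ worse by 0.83, false claims fall from 5.5% to 2.3% at 20% dilution. With a margin fixed at 0.83 they would rise from 2.5% to 4.1%.

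**The case against.** A reader might infer that the full analysis set is biased towards noninferiority, so that the optional per-protocol analysis removes the main protection. The documents do not support that. The margin comes from the same trial, so equal non-adherence shrinks the margin along with the difference and makes the claim harder, as shown above. The usual dilution argument would apply only with a margin fixed in advance.

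A reader might also infer that unblinded investigators will decide who is excluded for stress. The text does not say so. The phrase about investigators' judgement stands in the prohibited-drugs clause; nobody is named for stress events. Section 2.11 assigns the analysis to an independent statistician, and a full protocol or analysis plan, not shown, could require blinded classification. Unblinded classification is therefore a risk. It remains plausible because those who know of a stressful event, the participant and the treating investigator, know the group, while the blinded assessor does not see the records.

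It is also fair that the 70% compliance rule is objective (Section 2.8 bases it on counts of remaining drug), that exclusions from the per-protocol set cannot alter the full-set result, and that the 0.17-point example rests on assumed numbers. None of this justifies the stress exclusion itself, which is a stated rule and not a detail left to another document.

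**Conclusion.** The concern holds in a limited form. Section 2.11 makes the per-protocol analysis of a stated noninferiority aim discretionary, and defines the per-protocol set partly by an undefined, post-randomisation criterion linked to the outcome. Followed as written, that criterion can bias the per-protocol estimate in either direction. On the assumed exclusion of 3 of 56 participants, each 3 points below the mean, the shift is about 0.17 points, or 16 to 20% of an expected margin of 1.04 to 0.83. The bound for deliberate removal of the three worst is about 0.49 points. Neither selective exclusion nor a full-set bias towards noninferiority is established by the documents. No stated figure is wrong. The change is worth making because it is specific and cheap.

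**What to change.** In Section 2.11:

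1. Delete the exclusion for stress and other events that can cause digestive symptoms.
2. Limit per-protocol exclusions to objective items: compliance below 70%, prohibited drug use and eligibility violation. Have them classified blind to group before analysis.
3. Replace the conditional wording, so that the per-protocol analysis of Hypothesis 3 is always run and reported beside the full analysis set.
4. Test both sets against the same margin, and claim noninferiority only if the two agree. Without this, a data-derived margin would differ between the sets.

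The cost is wording plus one analysis already foreseen. The downside is a slightly stricter claim. That should be accepted knowingly, since with equally effective herbs the simulated chance of passing all three tests on one set is already only about 23% at 44/44/22 and 35% at 56/56/28.

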**Hypothesis** **1.**
*[*

$H_{0}\;:\;\mu_{1}=\mu_{2},\;H_{1}\;:\;\mu_{1}\neq \mu_{2}$

*]*

*-*

$\mu_{1}$

*: Change in TDS score of the YGJ group at week 6*

*-*

$\mu_{2}$

*: Change in TDS score of the usual care group at week 6*

A two-sided test with a significance level of 5% will be conducted using a mixed-effect model repeated measure (MMRM) with participants as the random factor and the treatment group and time of visit as the fixed factors. If necessary, analyses will be performed by setting variables showing statistically significant differences in demographic characteristics or variables that can affect dyspepsia as the fixed factors. The second purpose of this study is to evaluate the noninferiority of YGJ compared to that of PWS (Hypothesis 3). Consequently, the noninferiority margin (*M*) will first be defined based on the results of the effect evaluation of PWS compared to usual care at week 6 (Hypothesis 2), and the analysis method will be the same as that of Hypothesis 1.

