### 2.10. Sample Size Calculation

The primary objective of this study is to compare and evaluate the effectiveness of 6 weeks of administration of YGJ compared to usual care in participants with FD. We will test whether there is a difference in the degree of reduction in TDS scores between the two groups after 6 weeks through a superiority test. Based on the results of a previous study comparing YGJ and a placebo [19], and considering the 15% placebo effect, it is assumed that the difference between the average TDS change between the YGJ and usual care groups after 6 weeks is 2.70, and the standard deviation is 3.65. The significance level is 0.05, and the power is 80%. Taking into account the previous studies [11,19] and ethical issues, the ratio between the YGJ and usual care groups is assigned at 2:1. Therefore, 44 and 22 participants are required for the YGJ and usual care groups, respectively.

Additionally, the second purpose of this study is to evaluate the noninferiority of YGJ compared with that of PWS. For this, the noninferiority margin should be defined based on the results of the effect evaluation between the PWS and usual care groups. However, due to the lack of prior research and related data, we will first test the superiority of PWS compared to usual care after 6 weeks to define the noninferiority margin. Under the assumption that the effect size of the YGJ and PWS is the same, 44 participants are also required in the PWS group. Therefore, considering the 20% dropout rate, a total of 140 participants, including 56, 56, and 28 participants in the YGJ, PWS, and usual care groups, respectively, are required.

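### As worded, the primary model's random participant effect implies compound symmetry, so the week-6 standard error is valid only if the week-6 variance of TDS change equals the average over the modelled visits

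*Protocol article*

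**What the plan says.** Section 2.11, under Hypothesis 1, sets the primary analysis: "A two-sided test with a significance level of 5% will be conducted" with a "mixed-effect model repeated measure (MMRM) with participants as the random factor and the treatment group and time of visit as the fixed factors". The contrast of interest is the change in TDS at week 6, YGJ against usual care. Hypotheses 2 and 3 use the same method, also at week 6.

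The article does not list the visits that enter this model, and it neither states nor excludes a residual covariance structure. On measurement, the Abstract says "All participants will be assessed for clinical parameters at weeks 0, 3, 6, 9, and 24", and Section 2.9.2 and Table 1 confirm TDS at each of those times. Section 2.12, however, describes the week-24 telephone contact as data for the economic evaluation, collected after the 9-week effectiveness and safety trial has ended.

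The only variability figure is in Section 2.10: the assumed difference in "TDS change between the YGJ and usual care groups after 6 weeks is 2.70, and the standard deviation is 3.65". There is no SD for another visit, no SD by arm and no correlation between visits.

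**The concern.** A random participant effect with independent residuals gives every visit the same variance and every pair of visits the same correlation. The primary question concerns one visit, and the sample size rests on the SD at that visit. A model that borrows its variance from all visits answers the week-6 question correctly only if week 6 is typical of them.

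The design gives reason to doubt that. Two visits fall on treatment, one is three weeks after treatment ends, and one is a telephone contact 15 weeks after that. Change from baseline often becomes more variable as visits move away from baseline. If the averaged variance is too large, the test is conservative and loses power. If it is too small, the type I error exceeds 5%.

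The same standard error also sets the noninferiority margin, because Section 2.11 defines the margin as the lower 95% limit of the PWS comparison with usual care.

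**Working it through.** **Inputs from Section 2.10.** Difference 2.70, SD 3.65, two-sided alpha 0.05, power 80%, 2:1 allocation, and "44 and 22 participants are required for the YGJ and usual care groups, respectively".

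**The plan's own figure.** The two-sample normal formula with these inputs gives 22 usual care and 44 YGJ, so the stated size reproduces. Power at 44/22 is 80.9% by normal approximation and 79.7% by noncentral t. For dropout, 22/0.8 = 27.5, rounded to 28; 2 × 28 = 56; 56 + 56 + 28 = 140. None of this depends on the covariance model, because only the week-6 SD enters.

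**Formula.** With complete data and a group-by-visit mean model:
- true SE at week 6 = SD at week 6 × √(1/44 + 1/22) = 3.65 × 0.2611 = 0.953;
- random-intercept SE = √(mean of the visit variances) × 0.2611.

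With R = mean visit variance ÷ week-6 variance, the true type I error is 2 × [1 − Φ(1.96√R)]. Power is about 1 − Φ(1.96√R − 2.70/0.953), where 2.70/0.953 = 2.83.

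**Scenario A: correlation of raw scores decays with time (assumed).** Let the raw-score correlation be ρ per 3 weeks, with equal raw variances. The variance of change at week w is then proportional to 1 − ρ^(w/3).
- ρ = 0.9, weeks 3/6/9/24: 0.100, 0.190, 0.271, 0.570; mean 0.283. R = 0.283/0.190 = 1.49, type I error 1.7%, power 67%.
- ρ = 0.6: 0.400, 0.640, 0.784, 0.983; mean 0.702. R = 1.10, type I error 4.0%, power 78%.
- Weeks 3, 6 and 9 only: ρ = 0.9 gives 0.187/0.190 = 0.98 (type I error 5.2%, power 81%); ρ = 0.6 gives 0.608/0.640 = 0.95 (type I error 5.6%, power 82%).

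**Scenario B: variance peaks at week 6 (assumed SDs 3.2, 3.65, 3.3, 3.0).** The variances are 10.24, 13.32, 10.89 and 9.00, with mean 10.86. R = 10.86/13.32 = 0.815, type I error 7.7%.

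**Other assumed SD patterns, weeks 3/6/9/24.**

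| SDs | Model SE | Type I error |
|---|---|---|
| 3.65/3.65/3.65/3.65 | 0.953 | 5.0% |
| 3.0/3.65/3.9/4.2 | 0.970 | 4.6% |
| 3.65/3.65/4.5/5.0 | 1.107 | 2.3% |
| 2.5/3.65/3.65/3.65 | 0.888 | 6.8% |
| 2.5/3.65/3.0/3.0 | 0.800 | 10.0% |

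The last row is a deliberately sharp peak and marks the extreme.

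**Simulation check.** Mixed models were fitted to 300 simulated trials of 44/44/22 per pattern, with correlation decaying at 0.7 per visit. Rejection was 5.7% for equal variances (mean SE 0.946, empirical SD 0.944), 4.3% for 3.0/3.65/3.9/4.2, and 10.0% for 2.5/3.65/3.0/3.0. Monte Carlo error at 5% is √(0.05 × 0.95/300) = 1.3 points, so these agree with the formula.

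**Effect on the margin.** Suppose PWS beats usual care by the planned 2.70. The lower limit is then 2.70 − 1.96 × 0.953 = 0.83. With SE 0.800 it is 1.13, and with SE 1.107 it is 0.53.

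**Arm variances, a separate matter.** If variances are pooled over 44/44/22 and all arms share one SD, the ratio of model SE to true SE is 1.00. If the usual care SD is 1.2 times the herbal SD, the type I error is about 7.2%. If the herbal SD is 1.2 times larger, it is about 3.3%.

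**The case against.** The strongest reply is that the article names an MMRM, and that the residual covariance structure, the degrees-of-freedom method and the convergence fallback are commonly left to the full protocol or SAP, which are not shown. A random participant effect can be combined with a structured residual in SAS, and the phrase may be shorthand for participant as the clustering unit. That stands to this extent: the article does not say the random effect is the only covariance term, and missing detail is no fault. But the article is not silent on dependence. It states a term, and the usual unstructured covariance would replace that term, since it already absorbs a participant intercept.

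A reader might infer that the week-6 standard errors are wrong. The documents do not support that. They give no visit variances, and with equal variances of change the test is exactly nominal even when correlation decays.

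A reader might also infer that planned power will be lost. That needs week 24 in the model. Section 2.11 does not say it is, and Section 2.12 treats that contact as economic follow-up.

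Finally, the 2:1 allocation ("the ratio between the YGJ and usual care groups is assigned at 2:1") might be read as making the same flaw worse. It does not. Unequal arm sizes alone do no harm, and pooling variance across arms is not caused by a participant random effect: a common unstructured covariance pools the arms too.

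**Conclusion.** The point holds in conditional form. If the random participant effect is the whole covariance model, the week-6 standard error for Hypotheses 1 to 3 is valid only when the week-6 variance of TDS change equals the average over the modelled visits. The size and direction of any departure cannot be determined from the documents. Scenarios A and B bound the type I error at about 1.7% to 8%, with 10% under the sharpest peak tried. Every figure rests on assumed variances, complete data and a group-by-visit term. The article does not list that term; its absence is a separate question about the mean model. This is a worthwhile, inexpensive improvement to the primary analysis, not a demonstrated error in it.

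**What to change.** In Section 2.11, or in the SAP before unblinding, replace the random participant factor with repeated measures within participant under an unstructured covariance across visits and Kenward-Roger degrees of freedom. State which visits enter the model, and in particular whether week 24 does. State a fallback if the model does not converge; it should keep a separate variance for each visit, for example heterogeneous Toeplitz with sandwich standard errors. Take the week-6 contrasts for Hypotheses 1 to 3 from this model.

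The cost is one sentence and one SAS statement. The sample size is unchanged. The covariance parameters rise from 2 to 10 with four visits (4 × 5/2) or 6 with three (3 × 4/2). In simulation with equal visit variances, power was 80.3% against 80.6%, and a common unstructured covariance kept the type I error near 5% when arm variances were equal.

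An arm-specific covariance may be added as a sensitivity analysis. It costs about 1 point of power and matters only if arm variances differ.
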